### Power analyze

We hypothesize that there is a 15% absolute differences in efficacy between the groups, measured in clinical efficacy. We believe there to be an even bigger difference in bacteriological efficacy. Assuming an efficacy of 90 and 75% for 5 days and 3 days therapy, respectively, using a double-sided test with *p* < 0.05, and a statistical power of 0.8, we will need 113 patients in each group for the NTT analysis. With an estimated fall-out rate of app. 30% between each arm; 161 patients per group will need to be included for the PP analysis, and 230 in each group for the ITT analysis. There is a possibility for an interim analysis after 300 included participants, since we cannot reject a possibility for a higher (i.e. 20%) absolute efficacy.

## Data processing and statistical analysis

The source data is the GP’s and patient’s questionnaires and the diagnostics answers from the microbiological lab at the DCM. All source data will all be stored by the investigator and sponsor, in originals and scanned copies, at the DCM. The collected source data are transferred, logged and processed in the computers of the DCM. Analysis will be made in ITT, PP, and NTT form, respectively. All data will be analyzed coded, and only de-coded after the analysis is done and the analytic results are written in the relevant sections in the future article. The statistical software packages SAS (SAS Institute, Cary, NC) will be used for all analyses. Categorical data will be analyzed using a Fisher’s Exact test.

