### Study population

#### Inclusion criteria

Women in the age of 18–70 years old, with clinical features of community acquired uncomplicated LUTI, with the ability to understand the study and give consent, can participate. Patients need to have a symptom cumulative score of ≥2 p (i.e. none, mild, moderate or severe, scoring 0–3, respectively) in accordance to the validated questionnaires for uncomplicated UTI [16]. The following symptoms are included:Dysuria (i.e. pain or burning sensation when urinating)Urgency (i.e. feeling an increased and more frequent need to urinate)Pollakisuria/frequency (i.e. urinating more frequently than usually)

An accepted definition of uncomplicated LUTI is symptoms in concordance with uncomplicated LUTI and significant bacteriuria of uropathogenic bacteria [1], but we choose not to include the latter criteria in our intention to treat (ITT) analysis. This is because we want the included patients in the ITT group to mimic the realistic settings as much as possible (i.e. in which patients with uncomplicated LUTI will receive antibiotic therapy without urine samples in most primary care settings).

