### Day 0/inclusion

When consulting a patient examined and considered a suitable participant according to the inclusion and exclusion criteria, the GP will give the patient the opportunity to participate in the study. If the patient is still willing to participate, the patient will sign a form of consent with the GP, be scored by the GP on initial symptom load, and give a urine sample which will be sent with the questionnaire to the central laboratory and optionally examined with dipstick

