### Definitions

Clinically cured is defined as cumulative symptom score of <2.Clinical relapse is defined as initial clinically cured followed by cumulative clinical score of ≥2 at day 28.Bacteriologically cured is defined as significant reduction (i.e. ≥ 10^2^ fold decrease in uropathogenic bacteria) or potentially full eradication of uropathogenic bacteria (i.e. sterile culture or asymptomatic contaminations of non-uropathogenic bacteria).Bacteriological relapse is defined as initially bacteriologically cured followed by significant growth at day-28, with the same bacteria. Growth of other uropathogenic bacteria is defined as reinfection.

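### Day-4 clinical cure is to be compared with an unadjusted Fisher's exact test; the planned power is met, but a logistic analysis using the recorded day-0 symptom score would be modestly more efficient at almost no cost.

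*Protocol article*

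**What the plan says.** Under Data processing and statistical analysis, the protocol article names one test: "Categorical data will be analyzed using a Fisher’s Exact test". It mentions no covariate. The Primary endpoint section makes the day-4 clinical cure proportion part of co-primary endpoint 1 and the bacteriological cure proportion co-primary endpoint 2. Both are binary, so the sentence governs both.

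Three other sections bear on the clinical endpoint:

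- Inclusion criteria: "Patients need to have a symptom cumulative score of ≥2 p", over three symptoms each scored 0 to 3.
- Day 0/inclusion: the patient will "be scored by the GP on initial symptom load".
- Definitions, under Outcome: "Clinically cured is defined as cumulative symptom score of <2".

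The power section takes cure rates of 90% in the 5-day arm and 75% in the 3-day arm, a two-sided 5% level and 80% power. Its conclusion reads "we will need 113 patients in each group for the NTT analysis".

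**The concern.** Two features of the stated choice leave information unused for day-4 clinical cure.

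First, Fisher's test conditions on both margins of a discrete table. With these sample sizes its true error rate sits well below the nominal 5%, which costs power.

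Second, cure is a fixed threshold while entry scores may run from 2 to 9. A patient entering at 2 has to fall by one point to be counted as cured; a patient entering at 9 has to fall by eight. The entry score is therefore a natural candidate predictor of day-4 cure. It is recorded before treatment, but a comparison of raw proportions ignores it.

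What is at stake is efficiency, meaning the power and precision obtainable from patients who will be recruited anyway. The validity of the test is not in doubt.

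**Working it through.** **Inputs from the power section.** Cure 90% (5 days) v 75% (3 days), difference 0.15, two-sided 5%, power 0.80, 113 per group for the NTT analysis, 161 for PP and 230 for ITT. Equal allocation is assumed from the equal group sizes.

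**1. The plan's own figure.** With a mean rate of 0.825, the two-proportion formula gives

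n = [1.960·√(2·0.825·0.175) + 0.842·√(0.90·0.10 + 0.75·0.25)]² / 0.15² = (1.053 + 0.443)² / 0.0225 ≈ 99.5, so 100.

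The continuity correction gives

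n_c = (n/4)·[1 + √(1 + 4/(n·0.15))]² = (99.5/4)·(1 + √1.268)² ≈ 112.5, so 113.

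This matches the article exactly. The inflation also reproduces: 113/0.7 = 161.4 and 161/0.7 = 230.0. The corrected formula is the usual approximation for Fisher's test, so sample size and test agree.

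**2. Exact behaviour of Fisher's test.** This was found by enumerating both binomials. Power is for 90% v 75%.

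| n per arm | Fisher power | Uncorrected chi-square power | Gap (points) |
|---|---|---|---|
| 113 | 81.7% | 85.9% | 4.2 |
| 161 | 93.55% | 95.11% | 1.6 |
| 230 | 98.79% | 99.12% | 0.3 |

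Fisher's test first reaches 80% at about 110 per arm. At 113 per arm its true size is 2.8% at a common cure rate of 90%, 3.4% at 82.5% and 3.6% at 75%. The uncorrected chi-square has size 5.3%, 5.1% and 5.0% at the same rates. In sample-size terms, Fisher's conservatism costs 113 − 100 = 13 patients per arm at the NTT stage.

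**3. What the day-0 score adds by itself.** The article gives neither the prognostic strength of the score nor its distribution, so both are assumed. In simulations at 113 per arm (6,000 runs, 90% v 75%), likelihood-ratio tests from logistic regression without and with the score gave:

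| Assumed score distribution | Logit slope per point | Unadjusted | Adjusted | Gain (points) |
|---|---|---|---|---|
| Uniform 2–9 | 0.10 | 85.8% | 86.0% | 0.2 |
| Uniform 2–9 | 0.20 | 85.3% | 86.6% | 1.3 |
| Uniform 2–9 | 0.35 | 85.9% | 88.2% | 2.3 |
| Peaked mid-range | 0.20 | 86.3% | 86.8% | 0.5 |
| Peaked mid-range | 0.35 | 85.8% | 87.0% | 1.2 |

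With uniform scores, a slope of 0.20 means that 3-day cure falls from 86% at score 2 to 61% at score 9; a slope of 0.35 means a fall from 92% to 51%. The Monte Carlo standard error is about 0.45 points per estimate. If the score predicts nothing, the gain from adjustment is essentially nil.

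A cruder check divides n by (1 − R²), where R² is the share of outcome variance explained. Normal-approximation power at 113 then rises from 84.8% to 85.5% at R² = 2%, 86.6% at 5% and 88.3% at 10%, a gain of 0.7 to 3.5 points. This is the same order as the simulations.

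**4. Type I error of the adjusted test.** Simulated size was between 4.4% and 5.8%, so it is close to nominal, but unlike Fisher's it is not guaranteed to stay below 5%.

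**The case against.** The strongest reply is that nothing here is an error. The sample size carries the continuity correction, so Fisher's conservatism has been paid for and the test exceeds its 80% target. The covariate gain rests on invented slopes, and covariate adjustment may in any case be set out in a full protocol or analysis plan that is not shown. Most of this stands, and it limits the point to an improvement on a stated choice.

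Several stronger readings are tempting and are not supported:

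- **That planned power is lost.** It is not: 81.7% against 80%.
- **That adjustment yields the whole gain over Fisher's test.** About 4 points come simply from leaving the exact test; the score supplies only the remainder.
- **That speed of cure is left to an unsuitable test.** The sentence is limited to categorical data and does not assign Fisher's test to time to cure. A condensed article may leave the time-to-event method to the fuller document.
- **That no effect size will be available.** A risk difference can be reported beside Fisher's p-value, and nothing says that only p-values will be given.
- **That chance imbalance in entry score invalidates the result.** Allocation is randomised in blocks, and the test's error rate already allows for such imbalance.
- **That bacteriological cure would gain in the same way.** It is defined by culture, and the article gives no reason to expect the symptom score to predict it.

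What survives is that the article affirmatively names an unadjusted, conservative test for an outcome with a threshold-linked baseline score already in hand.

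**Conclusion.** The point holds as a minor efficiency improvement. For day-4 clinical cure, the named test is valid and adequately powered but runs at a true size of about 2.8% to 3.6% and leaves the day-0 score unused.

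At 113 per arm, moving off Fisher's test is worth about 4 points of power, falling to about 1.6 at 161 and 0.3 at 230. This part follows from the article's own figures. Adjustment is worth roughly a further 0 to 2.5 points at 113 per arm, and this part rests on assumed prognostic strength and score distribution. A strong predictor could give somewhat more and a weak one nothing. No gain from adjustment is claimed for bacteriological cure, and no fault is found over the analysis of time to cure.

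**What to change.** State that the primary analysis of day-4 clinical cure is a logistic regression with treatment and day-0 symptom score, reported as a standardised risk difference (5 days minus 3 days) with a 95% confidence interval. Specify that the covariate is the score given by the GP at inclusion, because the patient diary also starts on day 0 and the two could differ. Keep Fisher's exact test as a sensitivity analysis and for sparse tables, where its guaranteed error control is useful.

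The change should be fixed before the data are decoded. It needs no extra patients, visits or data. The cost is a few sentences of analysis wording, slightly more analysis work, and reliance on a large-sample test whose size is close to 5% rather than strictly below it.

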## Presentation of the results

Results (i.e. positive, negative and/or inconclusive) will be presented at scientific meetings, and in scientific publications in accordance to CONSORT 2010 statement [19].

## Ethical considerations

The study will comply with all the requirements to secure patients safety and to be carried out according to the Declaration of Helsinki, national laws and regulations. Ethical approval has been obtained by the Danish committee on biomedical research ethics for the capitol region of Denmark (No. H-4-2014-072). Approvals have also been obtained from the Danish National Health and Medicines Authority and the Danish Data Protection Agency. The study will be conducted according to the principle of Good Clinical Practice (GCP) and monitored by the GCP Unit of Bispebjerg Copenhagen University Hospital, Denmark. All patients will be included in concordance with rights of a research subject in clinical research, according to the national committee of health and research ethics document, which each subject will be provided the option to read before deciding to participate. The informed consent is obtained at the GP office, where the participant also will be informed about potential risks, benefits and procedures etc. based on an information sheet that the central investigators have prepared in concordance with above mentioned committees’ standards. The patient can withdraw their consent at any time without disadvantages.

### Data storage

The study will comply with the Danish regulation about management of personal information by the act on processing of personal data (Act No. 429 of 31 May 2000). All patient data will be carefully processed and stored at the Department of Clinical Microbiology, Hvidovre University Hospital, Denmark. All data will be anonymous in any possible future publication.

#### In trial intervention

The only time during the study in which we will intervene with antimicrobial therapy is if we during microbiological diagnostics find out that the patient is receiving a possibly ineffective therapy. This will for example be the case if we find causing uropathogenic bacteria to be:resistant to mecillinam (i.e. a small proportion of uropathogenic bacteria) [9]and/ora specimen to which pivmecillinam is not recommended for various reasons (non-susceptible, natural resistance etc.) - i.e. *Pseudomonas spp., Acinetobacter spp*., or *Enterococcus spp*. and other Gram positive uropathogenic bacteria etc.

We will then make contact and recommend another more suitable antimicrobial therapy.

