#### Intervention

All patients included will receive pivmecillinam therapy for 3 days or 5 days. The 3-day regimen group will receive blinded placebo tablets on day 4 and 5. If a secondary antibiotic treatment is required due to treatment failure (i.e. ongoing or worsening symptoms), a new antibiotic cure will be chosen in line with the results from the pre-treatment (inclusion day) urine culture. The GPs will be at any time welcome to call the Department of Clinical Microbiology (DCM) (i.e. central investigation site) for consultation in the matter.

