### Second medical consultation

Patients will be told at recruitment to visit the GP again if she develops worsening of symptoms or not experiencing any symptom relief during the study period. In that case the GP is able to choose a new treatment strategy for the patient and will have the potential microbiological diagnostic answers (i.e. from pre-treatment urine sample) to take in consideration in this approach.

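### Neither cure definition takes account of a new antibiotic before the assessment, so study-drug failures cleared by another drug count as cures in ITT and may be dropped from PP and NTT

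*Protocol article*

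**What the plan says.** **Cure.** Under Outcome, Definitions: "Clinically cured is defined as cumulative symptom score of <2". Bacteriological cure is a fall of at least 100-fold in uropathogens, or eradication. Neither definition refers to other antibiotics.

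**New antibiotics.** There are two routes.
- *Treatment failure.* The Intervention section provides that "a new antibiotic cure will be chosen in line with the results from the pre-treatment (inclusion day) urine culture". Under Second medical consultation, for worsening or unrelieved symptoms, "the GP is able to choose a new treatment strategy for the patient".
- *Laboratory finding.* Under In trial intervention, when the organism is resistant to mecillinam or of a species for which the drug is not recommended: "We will then make contact and recommend another more suitable antimicrobial therapy".

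**Timing.** The co-primary endpoints are clinical efficacy (speed of cure and proportion cured at day 4) and bacteriological cure at the first control urine. Microbiological diagnostics places that urine at day 8-10.

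**Who is analysed.** "Analysis will be made in ITT, PP, and NTT form, respectively". ITT is all included patients. PP is those with clinical and bacteriological follow-up data, without dropouts. NTT is the part of PP with significant bacteriuria and mecillinam-susceptible isolates. The termination criteria list treatment failure but not a laboratory-triggered switch.

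**The concern.** The trial compares two durations of one drug. A urine cleared by a different drug is no evidence for either duration, but the definitions as printed count it as such. The arm with more failures has more women to re-treat, so at an equal re-treatment share it gains more false cures. The error therefore runs towards no difference. That direction matters here, because the section on scientific and societal perspective envisages keeping the 3-day course if it proves non-inferior.

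The exposed endpoint is mainly the day 8-10 urine in ITT. Time to clinical cure is exposed less often. The day-4 proportion is exposed little, since a switch would have to happen and bring the score below 2 by day 4.

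**Working it through.** **Inputs from the Power section.** Cure rates are taken as 90% in the 5-day arm and 75% in the 3-day arm, with a two-sided 5% level and 80% power. The result is 113 per group for NTT. Fall-out is 30%, giving 161 per group for PP and 230 for ITT. The test is Fisher's exact.

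**Reproducing the plan.** The two-proportion formula gives 100 per group without, and 113 with, continuity correction. Then 113/0.7 = 161.4 and 161/0.7 = 230.0. Exact Fisher power at 90% v 75% is 0.82 at 113 per arm and 0.99 at 230.

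**1. Re-treatment for failure, ITT.** Let *p* be the true cure rate, *s* the share of failures re-treated before the control urine who still send it, and 0.9 the share of those who clear. Observed rate = *p* + (1 − *p*) × *s* × 0.9. The values of *s* and the 0.9 are assumptions.

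| *s* | 5 days | 3 days | Difference (points) | Fisher power, 230 per arm |
|---|---|---|---|---|
| 0 | 90.0% | 75.0% | 15.0 | 0.99 |
| 25% | 92.3% | 80.6% | 11.6 | 0.95 |
| 50% | 94.5% | 86.3% | 8.3 | 0.83 |
| 75% | 96.8% | 91.9% | 4.9 | 0.56 |

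Example, *s* = 50%: 0.90 + 0.10 × 0.45 = 0.945 and 0.75 + 0.25 × 0.45 = 0.8625.

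**2. Laboratory switch, ITT.** Let *r* be the share switched, with the same scored cure rate *c* in both arms. The difference is [(1 − *r*) × 0.90 + *rc*] − [(1 − *r*) × 0.75 + *rc*] = 15 × (1 − *r*) points, and *c* cancels. At *r* = 5% (the protocol's mecillinam resistance in *E. coli*; the share of other non-covered species is not given) it is 14.25 points whether these women are scored cured or not. Only the level changes: 90.5% v 76.25% if all are scored cured, 85.5% v 71.25% if none is. Fisher power at 230 per arm is 0.983 and 0.954 respectively; at *r* = 15% it is 0.967 and 0.828.

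**3. Failures terminated and excluded, PP and NTT.** If a share *g* of failures is dropped, the observed rate is *p* / [*p* + (1 − *p*)(1 − *g*)].
- *g* = 25%: 0.90/0.975 = 92.3% v 0.75/0.9375 = 80.0%, a difference of 12.3 points.
- *g* = 50%: 0.90/0.95 = 94.7% v 0.75/0.875 = 85.7%, a difference of 9.0 points.

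**The case against.** **The article is condensed, and a fuller document may score rescue antibiotics.** That is possible. But the cure definitions are printed as complete rules, and those rules misclassify an event that the same protocol plans for.

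**Scoring outcomes regardless of later treatment is a legitimate ITT strategy**, and it fits the stated wish to mimic real practice. This stands as a choice of estimand. The protocol does not say it makes that choice, and its stated aim is the efficacy of two pivmecillinam regimens. Such an analysis has a place as a sensitivity analysis.

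**Treatment failures are terminated, so they never reach PP or NTT as cures.** This is largely right. A reader might infer that re-treated women with susceptible isolates pass into NTT as cures; the termination criteria and the exclusion of dropouts point the other way. The risk in those sets is loss of failures (step 3). Their ITT status remains unstated.

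**The laboratory route does not bias the contrast.** Also right. A reader might infer from the switching rule that these women shrink the difference. Step 2 shows that the loss comes from enrolling women with such organisms, not from how they are scored, unless their cure on study drug alone differs by arm. Women with resistant isolates are outside NTT.

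**The rates are borrowed.** The 90% v 75% is stated for clinical efficacy, and the protocol expects a larger bacteriological difference. The re-treated shares have no source, and they require terminated women still to send a urine. The figures show scale only; at an equal share in both arms the direction does not depend on them.

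**Conclusion.** The point holds for ITT. The literal definitions count some study-drug failures as cures, and re-treatment for failure biases the bacteriological comparison towards no difference. On the assumed shares the difference is 11.6 to 4.9 points instead of 15, and power at 230 per arm is 0.95 to 0.56 instead of 0.99. With half of failures re-treated, power is still above the planned 0.80. A reader might conclude that the trial's power collapses more generally; the documents do not support that, because the misclassification falls mainly in ITT, the largest set.

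Laboratory-switched women are not on the termination list, so they can be scored as cures in PP as well as ITT. The fault there is an inflated cure rate, not bias between arms. In PP and NTT the larger worry is that failures are dropped: 12.3 or 9.0 points if 25% or 50% are lost.

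The window for a prior switch depends on when the first control urine is taken. Microbiological diagnostics says day 8-10, while the Outcomes part of the Discussion says day 4. The two must be reconciled.

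**What to change.** 1. Add to both cure definitions that a woman who has taken a non-study antibiotic active against uropathogens before an assessment is scored not cured at that assessment. For time to cure, she cannot be cured on or after the day of the switch.
2. State that women terminated or re-treated for treatment failure are kept as failures in ITT, PP and NTT, not excluded as dropouts.
3. Report outcomes regardless of new antibiotics as a sensitivity analysis.

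The cost is wording. The laboratory's own switch contacts, the planned follow-up calls and the day-28 questionnaire can supply the dates. Stated cure rates will fall slightly in both arms. Scoring laboratory switches as not cured costs some ITT power: 0.983 to 0.954 at 5% switched, and more if the share is higher (0.967 to 0.828 at 15%). Patient care is unchanged; the change concerns scoring only.

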### Adverse effects/risks

Pivmecillinam has been proven in RCTs to be safe and effective in the treatment of UTIs [6, 8, 20]. The risk off selecting and spreading off for mecillinam resistant bacteria is at very low risk [11], and mecillinam has a minor impact on the normal microflora [21]. Side effects are not more common than in any other penicillin, severe side effects are very rare, and the most common side effects are gastrointestinal complaints (i.e. nausea). Other common side-effects are rash and vulvovaginitis [6]. In the questionnaires the patients will be asked for possible adverse effects on day 1–7 and day 28. Any adverse reactions, serious adverse reactions or events during the study period will be reported according to GCP principles and in concordance with the Danish National Health and Medicine Authority.

